An extensive body of evidence supports the benefits of exercise in breast cancer survivors to improve treatment-related side effects such as physical function, body composition, quality of life, musculoskeletal symptoms or fatigue (16–18). However, Latina and Hispanic breast cancer survivors (LHBCS) are often underrepresented in exercise interventions, with only three studies involving these populations (16, 19, 20). We previously reported the benefits of high intensity interval training on cardiorespiratory fitness among breast cancer survivors (73% Latina or Hispanic) receiving anthracycline chemotherapy (21). Additionally, we reported the benefits of a 16-week supervised aerobic and resistance exercise intervention among breast cancer survivors (57% Latina or Hispanic) and found that ethnicity modified the effects of exercise on cardiorespiratory fitness (VO_2max)_, physical and emotional well-being, metabolic syndrome, and sleep quality (22–24). Given these findings, there is a pressing need for culturally tailored exercise interventions (e.g., bilingual study materials and staff, culturally sensitive educational and program components, and accessible delivery) among LHBCS to better understand how exercise can attenuate health disparities, improve health outcomes, and reduce disease burden beyond treatment (19).

Beyond the lack of representative exercise interventions, rates of participation in clinical cancer trials are low among disadvantaged and racial/ethnic minority groups (19, 25, 26), limiting the generalizability of results. It is imperative to bridge this research gap to address health disparities among the increasing number of LHBCS who experience poorer disease outcomes. Thus, we are currently conducting the ROSA trial, a randomized controlled trial to examine the effects of exercise on MetD in sedentary, obese LHBCS. We hypothesize that a 16-week supervised progressive aerobic and resistance exercise training program, followed by a 16-week unsupervised program will elicit improvements in MetD compared with the control group, and said improvements will be maintained among LHBCS during the 16-week follow-up (**Figure 1**).

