### 2.7 Outcome Measures

Testing is completed across two days at time points baseline (Week 0), post-phase 1 (Week 17), post-phase 2 (Week 33), and post-phase 3 (Week 49), with only one day required for testing at all mid-point assessments (Week 9, 25, 41). A complete data collection schedule is provided in **Figure 4**. All measures are collected at all time points and both groups unless specified below. Participants will be provided with monetary compensation (25$) for each testing timepoint attended, and parking validation for every visit to DFCI. All measures that have a verified Spanish version will be used for those who are Spanish speaking and/or would prefer to complete testing in Spanish.

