### 2.10 Statistical Analysis

The primary analysis population is all randomized subjects based on the intention-to-treat principle. The secondary analysis population is the per-protocol set. To test hypotheses related to differences in MetD outcomes across groups at the primary endpoint (4-month), we will use two-sample t-test for the continuous outcomes (HOMA-IR and VA) and Fisher’s exact test for the binary outcomes (diagnosis of metabolic syndrome). For HOMA-IR and VA, we will calculate change from baseline at 4-month for each subject and estimate mean difference between groups and corresponding 95% confidence interval. For diagnosis of metabolic syndrome, we will estimate the proportion of participants with metabolic syndrome at 4-month for each group and compare it between groups. Odds ratios and corresponding 95% confidence interval will be used to summarize the magnitude of the effect of the intervention. ANCOVA and logistic regression models will be also used to compare each of these outcomes at 4-month between groups, conditioning on potential prognostic factors, such as menopausal status, age, BMI, months since end of treatment, history of diabetes, type of treatment (chemotherapy vs radiation vs both), surgery type (lumpectomy, mastectomy), previous history of physical activity prior to diagnosis, and family medical history self-reported.

These primary endpoints are measured longitudinally. We will fit the longitudinal data with generalized mixed-effects models. The identical link and logistic link will be used for continuous and binary outcomes, respectively. The group indicator, time, and other covariates will be included in the models as the fixed effects. Some of the covariates (e.g., menopausal status) will be time-dependent covariates. Measures of physical fitness, functional capacity, and patient-reported QOL outcomes will be also analyzed in the same way.

Subgroup analyses will be conducted to assess the heterogeneity of the intervention effect on each outcome. The following factors will be considered: menopausal status, age, BMI, months since end of treatment, previous diabetes.

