## 3 Discussion

The ROSA trial is the first exercise oncology trial to focus on physically inactive LHBCS with obesity and comprehensively measured health outcomes. Specifically, this trial employs three phases of study period over 12 months: (1) we will determine the effects of 16-weeks virtually supervised progressive combined aerobic and resistance training on the primary outcome of MetD, a comprehensive health composite score (Phase 1); (2) Then, we provide a 16-weeks unsupervised home-based exercise program to support maintenance of exercise-induced health benefits from Phase 1 and to support exercise participation without direct supervision (Phase 2); and (3) Next, we examine whether exercise behaviors and changes in MetD outcomes can be maintained during a 16-week follow-up period when supervision and exercise programming is removed (Phase 3). Lastly, we will explore the effects of virtually supervised and unsupervised home-based exercise training on other important health markers such as physical fitness and function, cognition, and patient-reported outcomes.

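### The stated longitudinal model has no group-by-time term, so it gives no week-33 or week-49 effect and cannot test maintenance; the 4-month primary comparison is unaffected

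*Protocol article*

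**What the plan says.** The Introduction hypothesises improvement over control after the supervised and unsupervised phases, and that "said improvements will be maintained among LHBCS during the 16-week follow-up". The Discussion restates this as the Phase 3 question: "we examine whether exercise behaviors and changes in MetD outcomes can be maintained during a 16-week follow-up period".

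Section 2.10 describes two layers of analysis.

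- **At 4 months:** "we will use two-sample t-test for the continuous outcomes (HOMA-IR and VA) and Fisher’s exact test for the binary outcomes". ANCOVA and logistic regression follow for the same time point.
- **Over time:** "We will fit the longitudinal data with generalized mixed-effects models". The mean structure is then given: "The group indicator, time, and other covariates will be included in the models as the fixed effects". The next sentence adds: "Some of the covariates (e.g., menopausal status) will be time-dependent covariates".

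The paragraph ends by extending the approach to other outcomes: "Measures of physical fitness, functional capacity, and patient-reported QOL outcomes will be also analyzed in the same way".

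Section 2.7 sets visits at weeks 0, 9, 17, 25, 33, 41 and 49. DEXA, and so visceral adiposity, is measured only at weeks 0, 17, 33 and 49 (section 2.7.1).

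**The concern.** Maintenance is a statement about how the difference between arms changes from the end of the intervention to week 49. A model with group and time as main effects assumes that this difference does not change. It therefore presupposes the answer, and no coefficient in it estimates the week-49 difference or the change leading up to it.

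This matters for the second half of the trial hypothesis, for which no other analysis is described. It also matters for the later visits of the fitness, function and quality-of-life outcomes.

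Section 2.10 further relies on the longitudinal methods being valid when data are missing at random. That validity needs a correctly specified mean. If the effect differs by visit, the constant-difference model is misspecified, and dropout changes the weight each visit receives.

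**Working it through.** **1. The plan's own figure.** Section 2.9 gives 80 per arm, 15% attrition, SD of HOMA-IR change 6.9, difference 3.3 and two-sided alpha 0.05.

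- Evaluable per arm: 80 × 0.85 = 68.
- Standard error: 6.9 × √(2/68) = 1.183.
- Power: Φ(3.3/1.183 − 1.960) = Φ(0.829) = 0.796.

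The stated 80% reproduces. It belongs to the 4-month comparison and does not depend on the mixed model.

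**2. What the group coefficient estimates.** Take a continuous outcome, balanced data and a random intercept. With group and time as main effects, the group coefficient is the simple mean of the visit-specific differences:

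coefficient = (d₁ + … + d_k)/k

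This result does not depend on the within-person correlation.

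**3. Numbers.** Set the week-17 difference at 3.3. The trajectories are assumptions: zero at baseline, half effect at week 9, full effect from week 17 to week 33. After that the effect is either maintained to week 49, or halves at week 41 and is gone at week 49. The article does not say whether baseline is an outcome, so both cases are shown.

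| Visits fitted as outcomes | Maintained | Lost by week 49 |
|---|---|---|
| All seven | 5.5/7 × 3.3 = 2.59 (79%) | 4/7 × 3.3 = 1.89 (57%) |
| Six after baseline | 5.5/6 × 3.3 = 3.025 (92%) | 4/6 × 3.3 = 2.20 (67%) |
| Weeks 0, 17, 33, 49 | 3/4 × 3.3 = 2.475 (75%) | 2/4 × 3.3 = 1.65 (50%) |
| Weeks 17, 33, 49 | 3/3 × 3.3 = 3.30 (100%) | 2/3 × 3.3 = 2.20 (67%) |
| *True week-49 difference* | *3.30* | *0* |
| *True week 49 minus week 17* | *0* | *−3.30* |

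The percentages in the last two model rows also apply to visceral adiposity, which has only those visits.

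**4. Why the coefficient cannot answer the maintenance question.** With weeks 17, 33 and 49 as outcomes, true differences of 3.3, 3.3 and 0 give (3.3 + 3.3 + 0)/3 = 2.20. True differences of 2.2, 2.2 and 2.2 also give 2.20. The first is complete loss and the second is full maintenance, and the coefficient is the same.

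**5. What the interaction adds.** A small simulation used 60 runs, 68 per arm, weeks 0/17/33/49 and an assumed within-person correlation of 0.5. With group-by-visit fitted, true effects of 3.3, 1.65 and 0 came back as about 3.1, 1.5 and 0.0. The week-49-minus-week-17 contrast was rejected in 80% of runs when the effect was lost and in 2% when it was maintained. With so few runs these figures are approximate. They also assume 68 per arm at week 49, whereas section 2.9 gives attrition only for 4 months.

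**6. Limit of the arithmetic.** For metabolic syndrome, on the logit scale, the simple mean does not hold exactly. The structural point does: the model imposes one odds ratio at every visit.

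**The case against.** The strongest reply is that this is a journal article. The sentence names model ingredients rather than a formula; it does not say main effects only, how time is coded, or how baseline is handled. The full protocol or SAP may contain the interaction. That limits what can be concluded about the eventual analysis. But the article does state a list of fixed effects, and an interaction is not normally meant by other covariates. The stated model does not fit the stated aim, which is more than missing detail.

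Four stronger readings are tempting, and the document does not support them.

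- **That the main efficacy test is compromised.** The 4-month comparison has its own t-test or Fisher's exact test, plus ANCOVA or logistic regression, and the sample size rests on that comparison.
- **That the estimate is always diluted.** With only weeks 17, 33 and 49 as outcomes and a maintained effect, the coefficient is the full 3.30.
- **That time-updated BMI will adjust away part of the effect.** BMI is listed for the 4-month adjusted models. The only covariate named as time-dependent is menopausal status, for which the bias is probably small.
- **That time-dependent covariates help to defeat the maintenance test.** That failure comes from the missing interaction alone.

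The sentence on fitness, function and quality of life is also ambiguous. It may give those outcomes the 4-month tests as well, so the point is confined to their later visits.

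**Conclusion.** The point holds for the longitudinal model as the article states it. Without group-by-time, that model yields no week-33 or week-49 effect and no test of maintenance. The 4-month primary result stands apart from this.

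The structural conclusion needs no numerical assumption. Its size does: across the trajectories and visit sets shown, the coefficient runs from 50% to 100% of the week-17 effect, under balanced data and a random intercept. The trajectories are illustrative, not taken from the article.

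The time-dependent covariate wording is a secondary weakness. Conditioning on values observed after randomisation can distort the group effect. It also sits awkwardly with section 2.5, where menopausal status is a stratification factor evaluated at diagnosis.

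**What to change.** Restate the longitudinal model in section 2.10, or reconcile it with the SAP if that already has the term:

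- Fit visit as categorical with group-by-visit. Handle baseline as a covariate or constrain it to be equal across arms.
- Report the group differences at week 33 and week 49 with confidence intervals.
- Prespecify one maintenance contrast: week 49 minus a named end-of-intervention visit (week 17 or week 33). Judge it by its confidence interval, since a non-significant loss does not by itself show maintenance.
- Apply the same structure to the later visits of the fitness, function and quality-of-life outcomes.
- In any model that estimates the intervention effect, use pre-randomisation covariate values, with menopausal status as stratified.

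The cost is wording and a few more model parameters. No new data are needed and the sample size does not change.

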## 3 Discussion

The ROSA trial is the first exercise oncology trial to focus on physically inactive LHBCS with obesity and comprehensively measured health outcomes. Specifically, this trial employs three phases of study period over 12 months: (1) we will determine the effects of 16-weeks virtually supervised progressive combined aerobic and resistance training on the primary outcome of MetD, a comprehensive health composite score (Phase 1); (2) Then, we provide a 16-weeks unsupervised home-based exercise program to support maintenance of exercise-induced health benefits from Phase 1 and to support exercise participation without direct supervision (Phase 2); and (3) Next, we examine whether exercise behaviors and changes in MetD outcomes can be maintained during a 16-week follow-up period when supervision and exercise programming is removed (Phase 3). Lastly, we will explore the effects of virtually supervised and unsupervised home-based exercise training on other important health markers such as physical fitness and function, cognition, and patient-reported outcomes.

The ROSA trial targets an ethnic minority population of LHBCS who have been largely marginalized in previous research (19). The ROSA trial was designed in part by the results obtained from our previous trial (80). We previously reported that LHBCS had poorer physical fitness, and were younger and more likely to have advanced stage cancer compared with non-LHBCS breast cancer survivors. Additionally, among the same sample, we reported that LHBCS improved their metabolic profile more than non-Latina breast cancer survivors after 16-week supervised aerobic and resistance training (23). Moreover, our results showed that following the exercise intervention, LHBCS were more likely to experience larger benefits from exercise on physical and emotional well-being, cardiorespiratory fitness, and sleep quality compared to non-Latina survivors (22, 24). In addition to our trial, we found two previous studies focusing on exercise interventions in this specific population. Alexis et al. (81) reported that a home-based resistance and aerobic program improved muscle strength and range of motion in LHBCS. Moreover, the Project VIVA, found that LHBCS increase their levels of physical activity with exercise interventions that involved social support from family and friends (82). Therefore, given these findings and the lack of clinical trials in this population, we sought to conduct an exercise oncology trial solely focused on this vulnerable, highly understudied population to address the research gaps within exercise oncology.

The lack of inclusion of Latina and Hispanic populations in oncology research in general may be due to several reasons. In cancer screening, prevention, and treatment trials, unique barriers to recruitment of Latinas and Hispanics exist including lack of awareness in research, lack of transportation, interference with work/family responsibilities, financial costs, negative side effects, and burdensome procedures, such as required time to participate, having multiple jobs, caring for more than one generation of family members (83). Regarding exercise-oncology research, specific barriers to exercise reported by LHBCS include lack of enjoyment, lack of knowledge on how to exercise, feeling self-conscious due to physical appearance, and discouragement (84). Therefore, there is a need for investigating culturally tailored exercise intervention approaches, such as that utilized in the ROSA trial, that are effective at reducing said barriers, improving survivorship outcomes, and maintaining feasibility for LHBCS (85).

We selected MetD as the primary outcome of the ROSA Trial, which has been an emerging concern particularly among breast cancer survivors (86). MetD can develop or worsen after curative treatment for many cancers including breast, prostate, and testicular, and can negatively affect cancer outcomes as well as overall health status (87, 88). Further, in relation to the development of MetD, higher rates of metabolic-related comorbidities have been observed in patients with breast cancer who had completed treatments, with obesity present in 51% of cases, hypertension in 34%, peripheral vascular disease in 26%, and diabetes in 13% (89). As breast cancer survival rates continue to improve worldwide (90), there is increasing focus on the role of modifiable risk factors on prognosis. For example, obesity at diagnosis (91), metabolic syndrome (92), and insulin resistance at diagnosis (93), as well as hyperinsulinemia post-treatment (11), are associated with increased risk of breast cancer mortality, all-cause mortality, and breast cancer recurrence. Notably, there are ethnic disparities where the risk of developing MetD is 50% higher among Latinas and Hispanics than other ethnic groups (14, 94), increasing the need to reduce this co-morbidity in this minority population (95, 96). Although the presence of MetD specifically in LHBCS has not been reported either prior to diagnosis or during survivorship, our previous study showed that metabolic syndrome and central obesity were highly prevalent in LHBCS with 100% of LHBCS (n=40) with either metabolic syndrome or central obesity assessed within six months following completion of cancer-related treatments (22, 23). Therefore, the findings of the ROSA trial in exercise-induced changes in MetD are expected to provide significant evidence to reduce MetD in LHBCS. Reducing MetD in LHBCS may ultimately improve mortality and cancer recurrence rates, if the appropriate intervention is employed and sustained.

In addition to contributing to the scarce literature in health disparities in minorities, this randomized controlled trial also uses a novel approach with a virtually supervised home-based exercise intervention *via* Zoom to increase participant outreach and due to the COVID-19 pandemic. Winters-Stone et al. (97) found better adherence and retention rates with virtually supervised exercise compared with in-person exercise sessions. To our knowledge, the ROSA trial is the first study using this exercise approach in minority cancer survivors. Advantages of virtually supervised exercise interventions include the opportunity to increase accessibility reducing travel time and cost burden, decreasing non-essential person-to-person contact, reaching participants in rural settings, and maintaining an intact individualized exercise program not often utilized with telephone- or test-based interventions (98). Therefore, our findings will allow us to determine if this exercise approach may be effective to improve health outcomes and if it reduces barriers to participation in exercise trials in this specific population (84, 99).

There are several strengths of the ROSA trial. We use a randomized controlled trial design in a specific cancer minority population of LHBCS, focusing on high-risk breast cancer survivors with high rates of inactivity. Moreover, our exercise intervention is rigorously developed incorporating progressive combined aerobic and resistance training and is delivered virtually in Spanish or English by certified clinical exercise physiologists to enhance participants’ convenience and potentially adherence. There are several limitations of the ROSA trial. Our supervised intervention setting, despite the virtual format, may not be highly scalable into community settings due to the costs involving home exercise equipment and securing exercise trainers for supervised exercise sessions. Furthermore, we measure several outcomes, which may increase Type I error risk. Given the nature of an exercise intervention there is an intrinsic impossibility to blind participants and study stuff after randomization. Although our follow-up period would allow us to determine whether metabolic health status can be maintained during a 4-month follow-up, this short-period, along with our smaller sample size, would not permit us to capture if our exercise intervention may be associated with reductions in comorbidities, recurrence, or mortality. Lastly, our population of LHBCS is only representative of the New England area and does not represent LHBCS nationally or globally.

In conclusion, the ROSA trial will contribute to understanding a significant gap in the literature seeking to diversify exercise oncology research by targeting a cancer minority of LHBCS and by examining whether exercise is effective in improving MetD and whether these improvements are maintained post-intervention in LHBCS. Findings from this trial will help to understand how exercise may impact health-related outcomes that might translate into survival benefits. Lastly, understanding the barriers to participation in exercise clinical trials in underrepresented cancer populations may help the development of future exercise oncology guidelines and public health recommendations in physical activity with specific information for cancer minorities, thus reducing health disparities.

## Ethics Statement

The research protocol involving human participants were reviewed and approved by the Dana Farber Cancer Institute Institutional Review Board (IRB#20-221). Written informed consent will be obtained from participants to participate in the study. This clinical trial is registered in ClinicalTrials.gov (NCT04717050).

